#### Secondary outcome

Self-assessed mental health is measured by the mental health component scale of the SF-36 [61] at 1, 4 and 6 months.

#### Exploratory outcome measures

Register-based follow-up. Register data regarding mortality, causes of death, hospitalisation/re-hospitalisation, emergency room visits, outpatient visits, healthcare costs, visits to the general practitioner, medication use, employment status, and payment of welfare benefits (sick leave payment and early retirement pension) will be collected at 24 months to assess the long-term effect of the intervention (Table 1). Danish registers for the data mentioned above function well with only a small percentage of lost data [62]. Consequently the method is well suited as an outcome measure in small patient populations. Data will be extracted from the Danish National Patient Register [63], the Danish National Health Service Register [64], the Danish National Prescription Registry, the Danish National Causes of Death Register [65], and records of transfer payments and labour market affiliation [66,67].

Furthermore, the outcomes below will be measured at 1, 4 and 12 months following randomisation (Table 1). Questionnaires are also distributed at 6 and 24 months.

Six-minute walk test. The maximum walking distance (in meters) within 6 min is measured using standardised instructions [44], while subjective exhaustion with regard to fatigue and dyspnoe before and after using the Borg scale [55] is recorded.

Sit and stand test. The maximum number of times a patient can sit and rise from a normal chair within 30 s. Rate of perceived exertion is measured before and after using the Borg scale.

Biochemical screening. C-reactive protein (CRP), urea, glucose, haemoglobin, HbA1c, potassium, sodium, total cholesterol, creatinine, HDL cholesterol, LDL cholesterol and triglycerides. 1 EDTA plasma heparin tube will be frozen (80°) for further analyses (pro-brain natriuretic peptide and copeptin). The rationale for measuring cholesterol and triglyceride levels is to explore risk markers for cardiovascular disease for this patient group.

Questionnaires. The patient’s perceived physical and mental health will be analysed using relevant standardised questionnaires as mentioned in the objectives section (SF-36, HADS, QoL-CV, EQ-5D, HeartQoL, IPAQ and Emotion and Health Scale).

Echocardiography. Two-dimensional Doppler echocardiography will be performed with standard techniques (Philips iE33/ViCare, Denmark), corresponding to national and international guidelines for a full echocardiography [68] including valve function, with focus on diastolic function (E/A ratio), left atrial size (mm), and left atrial volume (mL). Data will be analysed blinded to randomisation group and time of echocardiography using EchoPac/Excelera.

### Economic evaluation

An economic evaluation will be conducted to assess the cost-utility of cardiac rehabilitation. The economic evaluation will compare the costs to quality-adjusted life years (QALYs), and take a societal perspective as recommended in Danish guidelines. QALYs and costs will be assessed at the end of the intervention 6 months from randomisation and later after 24 months from randomisation using register-based follow-up.

QALYs will be estimated using the self-completed EQ-5D instrument, which is a standardised instrument assessing five dimensions of self-reported health status (mobility, self-care, usual activities, pain/discomfort and anxiety/depression) [69,70]. The estimated calculations will be valued using Danish preference weights [71]. Information on costs will only include costs that are expected to differ between the experimental intervention and treatment as usual group [72]. Costs included costs in the evaluation are health costs associated with the rehabilitation programme, other healthcare costs (healthcare utilisation besides rehabilitation), patient costs, and costs of productivity losses. Information on costs will be collected by a mixture of activity-based costing, surveys, patient diary, and registers.

Results from the analysis will be reported as an incremental cost-effectiveness analysis (ICER). Sensitivity-analyses will be conducted to express uncertainty in the estimates [73]. The reporting of ICER is presented using Bayesian methods, including bootstrapping and presented as cost-effectiveness acceptability curves [74].

### Statistical analysis

SPSS version 17.0 and SAS version 9.3 will be used for the analyses. Data will be pseudo-anonymised and analysed blinded by a trial-independent statistician using intention-to-treat analyses, and a mixed model with repeated measures (MMRM) for continuous outcome measures [75]. Using MMRM ensures that missing data values (in the case of the primary and secondary outcomes) will not create bias as long as the values are missing at random. Two-sided tests are performed. The level of significance is set at 5%. Dealing with multiplicity, gate keeping will be used to adjust the observed *P* values for primary and secondary outcomes [76]. Both unadjusted and adjusted *P* values will be reported.

For the primary and secondary outcome measure, sensitivity analysis will be conducted to assess the potential impact of values missing not at random. For each intervention group (A and B) some quantities (imputing quantities) are computed to be used to impute missing values in a group (A or B) as explained as follows. A comparison between group A and group B where missing values in group A are imputed using imputing quantities obtained from group A and missing values from group B are imputed using imputing quantities obtained from group B is referred to as a best-case analysis. If missing values in group A are imputed using imputing quantities obtained from group B and *vice versa*, the comparison is called a worst-case analysis. The imputing quantities for the primary outcome are the group mean at T1 (X1-bar), the group mean at T4 (X4-bar), the group mean at T6 (X6-bar), the mean difference between the value measured at T4 and that measured at T1 (delta-1), and the mean difference between the value measured at T6 and that measured at T4 (delta-2). The quantities are used to impute missing values in a group (either the same group or the other intervention group) (Table 3). If the standard error (SE) of a parameter estimate calculated using imputed data is smaller than that of the corresponding parameter calculated using complete case data, it is replaced by the latter SE when the *P* value is calculated.

**Table 3 T3:** **The use of imputed values in CopenHeart**_
**VR**
_

**Observed pattern in group B at 1, 4 and 6 months**	**Imputed value in group B at 1 month**	**Imputed value in group B at 4 month**	**Imputed value in group B at 6 months**
mis^a^, mis, mis	X1-bar^b^	X4-bar^c^	X6-bar^d^
mis, mis, Y3^e^	Y3 - (delta^f^ + delta2^g^)^h^	Y3 - delta2	
mis, Y2, mis	Y2 – delta1		Y2 + delta2
Y1, mis, mis		Y1 + delta1	Y1 + delta1 + delta2
Y1, Y2, mis			Y2 + delta2
Y1, mis, Y3		(Y1 + delta1 + Y3 -delta2)/2	
mis, Y2, Y3	Y2 - delta1		

Table to explain the use of imputing quantities derived from observed values in a group (group A) to impute missing values in a group (group B).

^a^The value at 4 months is missing in group B.

^b^Mean of values observed in group A at 1 month.

^c^Mean of values observed in group A at 4 months.

^d^Mean of values observed in group A at 6 months.

^e^Observed value in group B at 6 months.

^f^The mean of difference between values observed at 4 months and value observed at 1 month in group A.

^g^The mean of difference between value observed at time 6 months and value observed at time 4 months in group A.

^h^If an imputed value is 0 it is set equal to 0.

Mis, Missing value; X1, Value at month 1; X4, Value at month 4; X6, Value at month 6.

Long-term register-based follow-up will be analysed by two different models: non-negative count outcomes (for example, number of contacts to hospital or number of visits to general practitioners) will be analysed by a Poisson model or a zero-inflated Poisson model if the number of zeros are large, and time-to-event data (for example, mortality and leaving the labour market) will be analysed with survival methods (Kaplan-Meier estimator and Cox regression model). Especially for socioeconomic outcomes, competing risks due to mortality will be considered if a large proportion of patients die during follow-up.

Exploratory outcome measures including data from the 6-minute walk test, ‘sit and stand’ test, biochemical screening and echocardiography will be analysed using appropriate statistical methods.

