### Trial procedure and randomisation

Patient inclusion was initiated on 17 February 2012, and recruitment is currently ongoing. Eligible patients are invited by a nurse or medical doctor to a short consultation on the second or third day after surgery, including distribution of written participant information. Patients needing further time to consider trial participation are contacted by phone 1 week after discharge.

At enrolment, on average 3 to 5 days after surgery, baseline data are collected (Table 1). A 6-minute walk test is performed as close to discharge as possible, using standard guidelines [44]. In case of postoperative complications after enrolment, such as pericardial exudate and atrial fibrillation, the patient’s case will be handled individually, and the intervention will be postponed according to recovery status. Participation in the trial will never delay usual medical follow-up.

**Table 1 T1:** Data collection

	**Baseline**	**1 month**	**4 months**	**6 months**	**12 months**	**24 months**	**Type of data**
*Background*							
Marital status	x						Categorical
Height, weight, body mass index	x						Continuous
*Medical history*							
History of heart disease	x						Binary
Diabetes mellitus	x						Binary
Kidney disease^a^	x						Binary
Chronic obstructive pulmonary disease (COPD)^b^	x						Binary
Hypertension	x						Binary
Dyslipidemia^c^	x						Binary
*Medicine*							
Use of medication, self-reported	x	x	x		x		Categorical
*Heart valve specific questions*							
Type of heart valve disease	x						Categorical
Type of heart valve surgery	x						Categorical
NYHA classification	x	x	x	x	x		Categorical
Left ventricle ejection fraction (LVEF)^d^	x	x	x				Continuous
Euro SCORE II^e^	x						Continuous
Postsurgical complications	x	x					Binary
Postsurgical arrhythmias^f^	x	x	x				Binary
Pacemaker post surgery	x	x	x				Binary
*Clinical measurements*							
Biochemical screening	x	x	x		x		Continuous
ECG		x	x				Binary
Echocardiography		x	x				Continuous
*Physical testing*							
Six minute walk test		x	x		x		Continuous
Cardiopulmonary Exercise Testing		x	x		x		Continuous
Sit and stand test		x	x		x		Continuous
*Questionnaires*							
Level of education	x			x			Categorical
Employment status	x			x			Categorical
Smoking	x			x			Binary
SF-36^g^	x	x	x	x	x	x	Continuous
HADS	x	x	x	x	x	x	Continuous
QoL-CV	x	x	x	X			Continuous
EQ-5D^g^	x			X	x	x	Continuous
HeartQoL	x			X	x	x	Continuous
IPAQ		x	x		x	x	Continuous

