Physical activity score	x	x	x	X	x	x	Categorical
Emotion and Health Scale	x			X			Continuous
Rehabilitation received^h^				X			Categorical
*Registry data assessment*							
Mortality, causes of death						X	Categorical
Hospitalisation						X	Continuous
Emergency room visits						X	Continuous
Outpatient clinic visits						X	Continuous
Contact with general practitioner						X	Continuous
Use of medication, register-based						X	Categorical
Employment status						X	Categorical

^a^Kidney disease: patient history of kidney disease.

^b^COPD: patient history of COPD, defined by FEV1 <70%.

^c^Dyslipidemia: total plasma cholesterol >5 mmol/L.

^d^At baseline: LVEF is pre surgery.

^e^European System for Cardiac Operative Risk Evaluation includes patient-related factors, cardiac-related factors and operation-related factors to calculate the predicted operative mortality for patients undergoing cardiac surgery.

^f^Atrial fibrillation, atrial flutter, malign arrhythmias.

^g^EQ-5D™ is a standardised instrument for use as a measure of health outcome from the EuroQoL group. ^h^Rehabilitation received: self-reported (Würgler MW *et al*. *Scand Jour Pub Health* 2012, **40:**126**–**132).

HADS, Hospital and Anxiety Depression Scale; HeartQoL, Heart Disease Health-Related Quality of Life; IPAQ, International Physical Activity Questionnaire; QoL-CV, Quality of Life Cardiac Version; SF-36, Short Form 36.

After collection of baseline data, central randomisation is conducted by telephoning the Copenhagen Trial Unit. The randomisation is stratified for left ventricular ejection fraction (≥45% or <45%), and type of valve surgery (sternotomy or percutaneous valve surgery, for example, catheter-based surgery), and not for the valve involved. Randomisation is conducted according to a computer-generated allocation sequence with a varying block size, concealed from the investigators to avoid selection bias. Thus, neither investigators and patients nor relatives can influence to which group the patients are allocated. Figure 2 shows patient flow throughout the trial.

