### Sample size and power calculation

We are performing a randomised trial with the continuous variable VO_2_ peak from independent control and intervention group participants as primary outcome with one control per intervention group participant. Previous studies report that VO_2_ peak is normally distributed in the intervention and control groups with a standard deviation between 4.0 and 9.3 mL/kg/min [14,15,20,21], though this might depend on the baseline peak VO2. However, if the true difference between the intervention and control group mean is 3 mL/kg/min [14,15,21], and the standard deviation is 6 mL/kg/min, inclusion of 105 participants is needed in the experimental intervention group, and 105 in the control group (a total of 210 participants) to be able to reject the null hypothesis, stating that the mean in the intervention and the control groups are the same with a power of 95%, and a type I error probability of 5%.

The secondary outcome measure is the continuous variable ‘mental health’. If the true difference between the intervention and control group is 7 points, and the standard deviation is 18 points [28,29], we will be able to reject the null hypothesis that the population means in the intervention and control group are equal with a probability of 80%, and a type 1 error probability of 5%.

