## Discussion

The major strength of The CopenHeart_VR_ is that it includes consecutive patients with a reasonable number of inclusion and exclusion criteria securing external validity for the results. The trial employs central, stratified randomisation, which secures against selection bias [77-79]. The primary outcome is assessed blinded to intervention, and so are all statistical analyses, which should reduce detection and interpretation bias [77-79]. The long-term outcomes are based on registry data, which are also likely not to include significantly biased reporting of outcomes.

The secondary outcome of self-assessed mental health is by nature subjective, and is likely to be biased [77-79]. The patients answer questionnaires independently of the researchers. All questionnaires are distributed electronically, thus data management is handled independently from the researchers that interpret data. All data are stored electronically in a coded database, and in an independent spread sheet, only accessible for the CopenHeart Group. The exploratory outcome measures highly impact the importance of this study as very limited knowledge exists concerning social and community outcomes for this patient group.

The limitations of the trial and methods used are similar to those of other trials including physical exercise and physical testing, which are time-of-day, and day-to-day variation in exercise testing [80]. To ensure standard testing of all physical exercise tests in the trial, standardised instructions for patients have been developed as described in the methods section. Including trial patients with left- and right-side heart valve surgery will result in an inhomogeneous trial population. Also, as peak VO2 is dependent on exercise capacity, age or recovery capacities, which differ according to the valve involved, consequently the expected results are going to depend on the recruitment. Conversely, the trial population will be representative of the broad heart valve population, and facilitate the external validity of The CopenHeart_VR_ rehabilitation programme in terms of daily clinical practice.

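### The secondary SF-36 analysis draws only on visits after randomisation; the baseline score already collected, and the two randomisation strata, should have a stated role in the models

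*Protocol article*

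**What the plan says.** All places are in the protocol article.

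- **Model (Statistical analysis).** Data are analysed "using intention-to-treat analyses, and a mixed model with repeated measures (MMRM) for continuous outcome measures". No fixed effects or covariates are listed, and none are ruled out.
- **Strata (Trial procedure and randomisation).** "The randomisation is stratified for left ventricular ejection fraction" (cut at 45%) and for type of valve surgery (sternotomy or percutaneous). Randomisation takes place once baseline data are in.
- **Secondary outcome.** "Self-assessed mental health is measured by the mental health component scale of the SF-36 [61] at 1, 4 and 6 months". The Objectives section fixes 6 months as its time point, and 4 months for peak VO2.
- **Table 1.** SF-36 is also marked at baseline. Enrolment and baseline collection fall on average 3 to 5 days after surgery.
- **Table 3.** The best-case and worst-case imputations use group means at months 1, 4 and 6 and mean changes between those visits. A patient missing at all three visits receives group means.
- **Psycho-educational component.** The nurse consultations start within the first month.
- **Walk test.** The enrolment text says "A 6-minute walk test is performed as close to discharge as possible". Table 1 and the exploratory outcomes section list it only at 1, 4 and 12 months.

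**The concern.** The trial records a pre-randomisation value of its own secondary outcome and then gives it no stated place in the outcome definition, the model or the imputation rules. Month 1 cannot stand in for it. It comes after randomisation, and in the experimental arm it may already carry an effect of the first consultation.

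The strata are in a similar position. They shape the allocation but have no stated place in the analysis. After stratified randomisation, an analysis without the strata is generally conservative: standard errors come out somewhat larger than they need to be.

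At stake is precision, mainly for the secondary outcome, which is planned at only 80% power. The all-missing row of Table 3 is also affected: it ignores what is known about the patient's own mental health at entry.

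**Working it through.** **Inputs from the document** (Sample size and power calculation; Statistical analysis). Primary: "if the true difference between the intervention and control group mean is 3 mL/kg/min", SD 6, 105 per arm, 95% power. Secondary: difference 7 points, SD 18, 80% power. "Two-sided tests are performed" at the 5% level.

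**Input not in the document.** The correlation ρ between the covariate and the outcome. A range is shown.

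**Step 1: reproduce the stated figures, unadjusted.** Power ≈ Φ(δ / (SD·√(2/n)) − 1.96), with √(2/105) = 0.1380.

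- Primary: (3/6)/0.1380 = 3.623; 3.623 − 1.96 = 1.663; power 95.2% (95.0% by the t-test). The sample size is 104 per arm by the normal approximation and 104.9, so 105, by the t-test.
- Secondary: (7/18)/0.1380 = 2.818; 2.818 − 1.96 = 0.858; power 80.4% (80.1% by the t-test).

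Both stated figures reproduce. They need no help from covariates.

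**Step 2: secondary outcome with baseline SF-36 as a covariate.** The residual SD becomes 18·√(1 − ρ²); the rest is unchanged. This treats the 6-month contrast as a covariate-adjusted comparison with complete data.

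| Assumed ρ | Residual SD | Power, 105 per arm | n per arm for 80% |
|---|---|---|---|
| 0 | 18.0 | 80.4% | 104 |
| 0.2 | 17.6 | 82.0% | 100 |
| 0.3 | 17.2 | 84.0% | 95 |
| 0.4 | 16.5 | 86.8% | 88 |
| 0.5 | 15.6 | 90.2% | 78 |
| 0.6 | 14.4 | 94.1% | 67 |

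Example at ρ = 0.5: 2.818/√0.75 = 3.254; 3.254 − 1.96 = 1.294; Φ = 90.2%.

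**Step 3: covariate, not change score.** A change from baseline has variance 2(1 − ρ)·SD² if the SD is the same at both times. At ρ = 0.3 that is 1.4·SD², and power falls to 66%. Change only breaks even at ρ = 0.5 (80.4%). The gain therefore depends on entering baseline as a covariate.

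**Step 4: the all-missing row of Table 3.** The same variances apply to the prediction error for a patient with only a baseline score, relative to SD². At ρ = 0.3 the group mean gives 1, baseline plus mean change gives 2(1 − 0.3) = 1.4, and regression on baseline gives 1 − 0.3² = 0.91. Regression never does worse than the group mean; adding a mean change can.

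**Step 5: primary outcome.** There is no pre-randomisation exercise test, so only the strata and other entry variables could help. At SD 6 power moves from 95.2% to 95.9% (ρ = 0.2), 96.7% (0.3), 97.7% (0.4) and 98.7% (0.5): at most about 3.5 points over this range. The document gives no figure for how much the strata explain.

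**The case against.** The strongest reply is that the article condenses a fuller protocol, any analysis plan is not shown, and covariates are what such documents usually hold. A reader might infer that the strata are left out of the model. The text does not support that: it lists no terms, and silence is not exclusion. On the strata the point is therefore a request to state them. Baseline SF-36 is different, because the outcome definition and Table 3 do list their visits, and baseline is not among them. (The text labels the imputing quantities as those of the primary outcome. The section introduces the scheme for both outcomes, however, and month 6 is an SF-36 visit and not an exercise-test visit in Table 1, so I read it as covering SF-36.)

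Other stronger readings are also not supported:

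- **The trial is underpowered or biased without adjustment.** Step 1 shows otherwise, and an unadjusted comparison is valid under randomisation.
- **Month 1 is used as a baseline.** Nothing says so; it is listed among the outcome visits. For peak VO2, training begins only after the month-1 test, so contamination there is less likely than for SF-36.
- **Covariates would rescue early dropouts.** A patient with no outcome value adds nothing to a standard MMRM with baseline as a covariate. Covariates can make the missing-at-random assumption more plausible, but they do not bring that patient in.
- **Walk distance is a ready covariate.** The Discussion does say "as peak VO2 is dependent on exercise capacity, age or recovery capacities, which differ according to the valve involved", which makes a fitness measure attractive. But the early walk test is timed to discharge, not to randomisation, and Table 1 shows no baseline walk test.

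It is also fair to say that a score taken days after surgery may predict month 6 poorly. That stands, and is why the range starts at 0.2.

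**Conclusion.** The point holds as a free improvement in efficiency. A pre-randomisation SF-36 is collected and has no stated role in the secondary analysis or in Table 3. Using it would raise secondary power from about 80% to somewhere between 82% and 94% for correlations of 0.2 to 0.6. The document supports no particular value in that range, and the lower end is quite possible. The primary gain is small at SD 6. The planned sample size and both stated powers are correct as they stand.

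**What to change.** State the following before unblinding:

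1. Both MMRMs include the LVEF stratum and the surgery-type stratum as fixed effects.
2. The secondary model adds baseline SF-36 mental component score and its interaction with visit, as a covariate and not as a change score. Add a rule for a missing baseline score, so that no randomised patient with follow-up is dropped.
3. Month 1 stays a response in both models. The tested contrasts remain those in the Objectives: 4 months for peak VO2, 6 months for SF-36.
4. For SF-36 in Table 3, the row with all follow-up missing uses the patient's own baseline. One form is (group mean at the visit) + b × (own baseline − group mean at baseline), with b and the means taken from whichever group supplies the imputing quantities.
5. Reconcile the enrolment text with Table 1 on the early walk test. Use it as a covariate for peak VO2 only if it is confirmed to precede randomisation.

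Items 1 to 4 cost wording only; the strata and the baseline SF-36 are already collected. Item 5 needs a check of when the test was done.

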## Abstract

**Background:**

Heart valve diseases are common with an estimated prevalence of 2.5% in the Western world. The number is rising due to an ageing population. Once symptomatic, heart valve diseases are potentially lethal, and heavily influence daily living and quality of life. Surgical treatment, either valve replacement or repair, remains the treatment of choice. However, post surgery, the transition to daily living may become a physical, mental and social challenge. We hypothesise that a comprehensive cardiac rehabilitation programme can improve physical capacity and self-assessed mental health and reduce hospitalisation and healthcare costs after heart valve surgery.

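### The Poisson or zero-inflated Poisson rule for the exploratory 24-month register counts makes no allowance for contact rates that differ among patients who use care, so standard errors are too small if the counts are overdispersed

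*Protocol article*

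**What the plan says.** The Statistical analysis section of the protocol article divides the long-term register outcomes into counts and time-to-event data. The counts are described as "non-negative count outcomes (for example, number of contacts to hospital or number of visits to general practitioners"), and they "will be analysed by a Poisson model or a zero-inflated Poisson model if the number of zeros are large". No other model is named for them, and many zeros is the only stated condition for leaving plain Poisson.

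The section Exploratory outcome measures lists the register outcomes, among them "hospitalisation/re-hospitalisation, emergency room visits, outpatient visits, healthcare costs, visits to the general practitioner". These data "will be collected at 24 months to assess the long-term effect of the intervention".

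On testing, the Statistical analysis section states "Two-sided tests are performed" and sets a 5% level. Gatekeeping covers only the primary and secondary outcomes. The register outcomes carry no multiplicity control, and the Objectives section places healthcare utilisation among the exploratory analyses. The Background paragraph of the Abstract nevertheless includes in the trial's hypothesis that rehabilitation can "reduce hospitalisation and healthcare costs after heart valve surgery".

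**The concern.** A Poisson model forces the variance of a count to equal its mean. That holds only if all patients in an arm with the same follow-up share one contact rate. Zero-inflated Poisson adds a group who can never have a contact, but still assumes one common rate among everyone else.

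The trial enrols adults of any age from 18, with right- or left-sided valve surgery, by sternotomy or catheter, with ejection fraction above or below 45%, and with comorbidities such as diabetes, kidney disease and COPD recorded at baseline. The Discussion itself calls the population mixed. Two-year contact rates can be expected to differ between such patients. If they do, the counts vary more than Poisson allows and the model-based standard errors are too small.

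At stake are the P values and confidence intervals for healthcare use. Several counts will be tested, and the nominal 5% level is their only protection against a chance finding. The Discussion gives the exploratory outcomes considerable weight in the trial's importance.

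**Working it through.** **Inputs from the article.** 1:1 allocation, 105 per arm, two-sided 5% tests. The article gives no mean, variance or dispersion for any count, so those are assumptions below.

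**The plan's own figure.** The sample size rests on the primary outcome only: n per arm = 2 × (1.960 + 1.645)² × 6² / 3² = 104 after rounding up, and 105 per arm gives 95.2% power. The stated 105 is reproduced. There is no stated design figure for the counts to reproduce.

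**Formula.** Let φ be the ratio of variance to mean. The Poisson model-based standard error is then 1/√φ of the true one, and the actual two-sided error of a nominal 5% test is 2 × [1 − Φ(1.96/√φ)].

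| φ | Model SE as share of true SE | Actual type I error |
|---|---|---|
| 1.2 | 91% | 7.4% |
| 1.5 | 82% | 11.0% |
| 2 | 71% | 16.6% |
| 3 | 58% | 25.8% |
| 5 | 45% | 38.1% |

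For example, at φ = 2: 1.96/√2 = 1.386, and 2 × [1 − Φ(1.386)] = 16.6%.

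**Simulation under no effect.** 105 per arm, Poisson counts with gamma-distributed patient rates, so variance = mean + k × mean² and φ = 1 + k × mean. The expected share of zeros is (1 + k × mean)^(−1/k). There were 3,000 runs for the Poisson and robust Wald tests, and 300 for the zero-inflated Poisson likelihood-ratio test (common inflation probability, count mean differing by arm).

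| Mean | k | φ | Zeros | Poisson | Zero-inflated Poisson | Poisson, robust SE |
|---|---|---|---|---|---|---|
| 1 | 0.25 | 1.25 | 41% | 8.0% | 4.7% | 5.2% |
| 1 | 0.5 | 1.5 | 44% | 10.5% | 8.7% | 5.2% |
| 2 | 0.5 | 2 | 25% | 17.3% | 14.0% | 5.5% |
| 2 | 1 | 3 | 33% | 25.1% | 21.3% | 5.2% |
| 2 | 2 | 5 | 45% | 38.2% | 32.7% | 6.0% |
| 4 | 1 | 5 | 20% | 37.9% | 32.7% | 5.5% |
| 15 | 0.5 | 8.5 | 1.4% | 50.7% | not triggered | 5.6% |

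Monte Carlo error (95%) is about ±1.5 points for a Poisson figure near 25% (1.96 × √(0.25 × 0.75/3000)) and about ±4.6 points for the zero-inflated figure of 21.3% (1.96 × √(0.213 × 0.787/300)).

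**Which model the rule would pick.** At mean 2 and k = 1, 33% zeros are expected against e^(−2) = 13.5% under Poisson, so the rule could well select zero-inflated Poisson, and 21.3% is then the relevant figure. At mean 15 and k = 0.5 only about 1.4% are zeros, so plain Poisson stays in force.

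**Does a remedy work?** Over all 20 scenarios run (means 1 to 15, k 0.25 to 2), robust standard errors or a Pearson-scaled quasi-Poisson model gave 4.6% to 6.8%. Negative binomial regression, at 300 runs per scenario, gave about 3% to 8%; Monte Carlo error at 5% is about ±2.5 points.

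**The case against.** The strongest reply is that the article names a model family and not a variance estimator. Poisson regression with robust variance is still a Poisson model, and variance options, dispersion checks and offsets are commonly left to an analysis plan that is not shown. This stands in part: the text does not forbid robust variance, and the missing offset alone would not be a finding. But the section does more than stay silent. It names two models and one rule for choosing between them. In the next paragraph it leaves other exploratory outcomes to unspecified suitable methods, so for the counts a choice was made. A rule that looks only at zeros cannot detect differing rates among users of care.

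Second, the size is assumed. This stands. For rare events with mild heterogeneity, as emergency visits or readmissions might be, Poisson gives 8 to 11% and zero-inflated Poisson can be nominal. A reader might infer that every register count would be tested at several times 5%; the documents give no dispersion that would support this.

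Third, zero-inflated Poisson does absorb overdispersion that comes from excess zeros. This also stands, so it would be wrong to say that both models ignore overdispersion altogether.

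Fourth, the outcomes are exploratory. This stands and limits the consequence.

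Finally, a reader might suspect bias because the model is chosen after the zeros are seen. The article has a trial-independent statistician analyse blinded data, so that reading is not supported.

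**Conclusion.** The point holds as a conditional one. The stated rule gives standard errors and confidence intervals that are too narrow whenever contact rates differ among patients who use care. The direction is certain under that condition. The size depends on a dispersion that the article does not give: with Poisson, roughly 1.5 to 2 times the nominal 5% at a variance-to-mean ratio of 1.2 to 1.5, and more than three times once the ratio reaches 2. Where zeros are many enough for zero-inflated Poisson to be chosen, the excess shrinks but does not vanish unless counts are rare and only mildly dispersed. The figures assume gamma-distributed patient rates and full follow-up of 105 patients per arm.

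A reader might also infer that the trial's main conclusions are at risk. They are not: peak VO2 and the SF-36 mental component use a different model and are protected by gatekeeping. Healthcare costs are not affected either. They are not counts, and the Economic evaluation section handles their uncertainty separately with sensitivity analyses and bootstrapping. What is affected is any claim about reduced hospital, emergency, outpatient or GP contacts, which matters because less hospitalisation is part of the stated hypothesis.

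**What to change.** Replace the count-model sentence with one that makes Poisson regression with robust (sandwich) variance, or negative binomial regression, the main model for all register counts. Name one of the two before the register data are opened. Include log follow-up time as an offset so that patients who die before 24 months contribute their actual time at risk. Keep plain Poisson and zero-inflated Poisson as sensitivity analyses. The change does not apply to healthcare costs.

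The cost is one sentence and a standard software option. Confidence intervals become wider when counts are overdispersed. If the counts turn out to follow a Poisson distribution, robust variance gives nearly the same interval, so little is lost.
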